#### Learning collaborative

All clinics receiving provider-focused strategies will be invited to join a learning collaborative [65], called “HeartBEAT (Blood pressure Equity Action Team),” organized by external facilitators. Learning collaboratives gather representatives from multiple implementation sites for shared learning and problem-solving. In HeartBEAT, quarterly meetings of clinic champions and leadership will focus on how clinics are working toward hypertension equity; between meetings, clinics will use quality improvement strategies like PDSA cycles to enact desired practice and policy changes. Furthermore, nurse facilitators will offer provider-focused technical assistance through monthly office hours.

#### Blood pressure care clinic champion

The Blood Pressure Care Clinic Champion is a staff member who becomes a clinic expert in best practices for implementing evidence-based, culturally tailored, equitable hypertension care within LAC DHS and serves as a liaison between the clinic and the study to support clinic change. The Champion will give clinic leadership regular project updates, meet monthly with the clinic’s assigned external or nurse facilitator, distribute and monitor use of culturally tailored materials, contribute information to support quarterly completion of the intervention fidelity checklist, participate in HeartBEAT meetings to share learnings on EBP delivery, and disseminate lessons among the clinic’s staff and leadership.

#### Resource guide and provider-focused clinic poster

We developed written materials to reinforce EBP adoption. Posters placed in clinics in the provider-focused strategy arm summarize tools for EBPs. A Resource Guide highlights local resources and summarizes step-by-step workflows for LAC DHS. As with posters developed for the patient-focused strategies arm, the provider-focused posters incorporate behavioral science by promoting social norms of hypertension care.

### Outcomes

We identified key implementation outcomes using the RE-AIM [66] framework (Table 4). The primary implementation outcome is overall provider EBP adoption clustered at the clinic level, determined using a scoring system derived from EHR data, LAC DHS administrative data, LAC DHS Patient Outreach Center data, the patient portal, and registration logs for hypertension training sessions. The main health-related outcome will be proportion of patients within a clinic with controlled hypertension by race and ethnicity. The definition of adequate blood pressure control is blood pressure < 130/80 [69]. We will also use an alternative, more stringent threshold, such as blood pressure < 120/80, since studies suggest that patients with established atherosclerotic cardiovascular disease assigned to lower targets have lower rates of cardiovascular events or death compared to those assigned to standard targets [67, 70, 71]. The data source will be LAC DHS’s EHR. Finally, we will track community engagement activities and new collaborations through discussions with and surveys of LAC DHS leadership and managers, Steering Committee members, and CAB members.

**Table 4 Tab4:** Implementation and Effectiveness Outcome Measures, Data Sources, and Data Collection Time Points

Domain	Measure	Target	Data Source	Timing During Implementation			
					**Implementation**		**Sustainment**
				**Year 0**	**Year 1**	**Year 2**	**Year 3**
**Reach**							
Patient population coverage	% of eligible clients receiving EBP^a^		EHR	**✓**	**✓**	**✓**	**✓**
Disparities in coverage	Rates of EBP receipt by patient race and ethnicity		EHR	**✓**	**✓**	**✓**	**✓**
**Effectiveness**							
BP control^b^	AHA/ACC Guidelines		EHR	**✓**	**✓**	**✓**	**✓**
Secondary outcomes^b^	AHA/ACC Guidelines		EHR	**✓**	**✓**	**✓**	**✓**
**Adoption**							
Provider adoption^a^	See scoring system (Table 6)	Provider	EHR and Online Provider Survey	**✓**	**✓**	**✓**	**✓**
**Implementation**							
Acceptability, appropriateness, and feasibility^b^	Adapted Acceptability of Intervention Measure (AIM); Intervention Appropriateness Measure (IAM); Feasibility of Intervention Measure (FIM) [43]	Provider	Online Provider Survey, Periodic Reflections	**✓**	**✓**	**✓**	**✓**
Delivery and quality of implementation strategies^b^	Stages of Implementation Completion (SIC) [67]	Provider	SIC dashboard, Periodic Reflections		**✓**	**✓**	**✓**
Implementation costs (e.g., provider time, incentives, training, EHR updates)^b^	Costs of Implementing New Strategies (COINS) [68]; other Cost Instruments	Provider	SIC AND COINS dashboard		**✓**	**✓**	
**Maintenance/Sustainment**							
Clinician intent to maintain intervention component^b^		Provider	Online Provider Survey			**✓**	
Sustainment of reach, adoption, effectiveness, implementation outcomes^b^		Provider	Online Provider Survey				**✓**

*EBP* Evidence-based practice, *BP* Blood pressure, *EHR* Electronic health records, *AHA*, American Heart Association, *ACC* American College of Cardiology

^a^ Primary Outcome

^b^ Secondary Effectiveness Outcomes include health-related outcomes, disparities, and sustainment

### Data collection

#### Masking

We developed a detailed masking protocol that describes data access for different research team members (Principal Investigators, Co-Investigators, Project Coordinator and Director, Facilitators, Statisticians, Data Managers, and Data Analysts). Data includes clinic and provider study arm assignment, clinic-level stages of implementation, EHR data, provider surveys, and clinic-, provider-, and patient-level administrative data (e.g., webinar participation). For example, an unmasked data analyst who knows study arm assignment of clinics will obtain, clean, and harmonize EHR data, while a separate masked statistician/data analyst will conduct analyses for primary and secondary outcomes.

#### Provider survey

The annual provider survey begins with demographic characteristics, training, years worked in the clinic, and overall impression of the clinic’s approach to hypertension management. Subsequent sections ask about the eight EBPs. Each section describes an EBP before asking the provider whether they followed the EBP in the past 12 months, how successful EBP implementation was, and how often they expect to follow the EBP in the next 12 months; each section also solicits ratings for acceptability, appropriateness, and feasibility of the EBP, using questions adapted from the Acceptability of Intervention Measure, Intervention Appropriateness Measure, and Feasibility of Intervention Measure, respectively [68].

#### Clinic EHR

We will extract annual, de-identified blood pressure data from the EHR, using NCQA HEDIS specifications, for eligible adult patients (> 18 years) with hypertension seen in participating clinics [39]. We will collect date, location, time, and value of measurement. In cases with multiple measurements on one day, we will record them all and average the values [72].

#### Implementation progress

External facilitators will monitor and record progress toward implementing EBPs using the SIC [52], a web-based tool for monitoring implementation delivery and quality that can be customized to track relevant activities. The SIC will track dates and completion of activities across Implementation (staff hired and trained, fidelity monitoring, consultation, ongoing services) and Sustainment phases. The SIC allows facilitators to track progress and actively intervene when concerns arise, as implementation is more likely to be successful when activities are completed thoroughly and quickly. The SIC will provide metrics of implementation progress for each clinic, such as number of implementation activities completed, which will help contextualize primary and secondary implementation outcomes.

#### Intervention-related costs

We will use the Cost of Implementing New Strategies (COINS) [73], a tool embedded within the SIC, to map costs and resource use (e.g., personnel time) onto implementation activities. When analyzing COINS data, we will work with LAC DHS leadership to establish appropriate personnel and resource costs. For example, facilitators will track time spent on various activities, and LAC DHS will provide hourly rates for that time by role. We will summarize implementation costs by trial arm.

#### Partnership sustainment and community engagement

For our quarterly Steering Committee Meetings, weekly LAC DHS Health System Partnership meetings, and quarterly CAB meetings, we will document discussions, including feedback on implementation strategies, progress, challenges and successes, reflections on partnerships, sharing of study-generated patient and provider materials, and interpretation and dissemination of results.

#### Data management

Clinic-level data will be encrypted and stored on a secure UCLA server, while patient-level data will be stored and analyzed on a secure LAC DHS server. Only approved study team members will have access to identifiable data. After study completion, de-identified data will be transmitted to and stored for use by outside researchers at the Data Center of the Research Coordinating Center (RCC), a hub that manages the operational and administrative aspects of the DECIPHeR Alliance [74]. Rather than being transferred to the RCC, patient data will be maintained at LAC DHS and analyzed using code developed by the RCC.

#### Statistical analysis

We will generate baseline descriptive statistics and frequencies for demographic, clinical characteristics, and outcome measures for all participants (providers and patients) by implementation arm and by race or ethnicity. We will use an intent-to-treat approach, i.e., we will include all participating providers from participating clinics. We do not plan interim analyses.

#### Primary outcome analysis

The primary implementation outcome, provider EBP adoption clustered at the clinic level, uses a scoring system to evaluate overall adoption of the modified EBP components (Table 5). Scores range from 0 to 9, with higher scores indicating higher EBP adoption. The primary objective is to compare changes in event rate of provider EBP adoption between usual implementation strategy (Arm 1) and provider- and patient-focused strategies (Arms 2 and 3) at the end of Year 1, using the constrained generalized Poisson mixed-effects model. This analytical approach [50] has been shown to be more efficient than traditional longitudinal models for estimating group differences at follow-up when baseline values are missing. The main fixed effects include a time indicator, a constraint of a common baseline mean across implementation groups, and a group-by-time interaction term. The model also includes random intercepts at bothprovider and clinic levels, as well as a clinic-level time-varying random effect to account for various levels of clustering and repeated measures. Analyses on provider-level implementation outcomes will be based on available data, as we expect low levels of missing data (< 3%) for the primary implementation outcome.

**Table 5 Tab5:** Provider Evidence-based Practice Adoption Score (Primary Implementation Outcomes)

Component	Data Source	Component eligibility	Scoring
1. Home BP monitor documented or acquired	EHR and clinic surveillance	Patients with uncontrolled HTN empaneled to provider	0: < 30% pts 1: ≥ 30% of pts
2. Home BP readings uploaded onto the patient portal	EHR	Patients with uncontrolled HTN empaneled to provider	0: < 30% of pts 1: ≥ 30% of pts
3. Primary care visit attended within 1–12 weeks of uncontrolled BP^1^	EHR	Patients with uncontrolled HTN empaneled to provider	0: < 50% of pts 1: ≥ 50% of pts
4. HTN clinic nurse visit attended within 1–12 weeks uncontrolled reading^1^	EHR	Patients with uncontrolled HTN empaneled to provider	0: < 30% of pts 1: ≥ 30% of pts
5. Referral of patients to HTN resources (via texts, portal, mailings, phone calls)	EHR, Patient referrals	Patients with uncontrolled HTN empaneled to provider	0: < 50% of pts 1: ≥ 50% of pts
6. Social needs screening conducted	EHR	Patients with HTN empaneled to provider	0: < 50% of pts 1: ≥ 50% of pts
7. CHW assigned and met with patient	EHR	Patient with HTN with identified social needs empaneled to provider	0: < 30% of pts 1: ≥ 30% of pts
8. Uptake of HTN education and training	Course participation and CME requests	All providers	0: 0 class attended 1: ≥ 1 classes attended
9. Combination medications prescribed	EHR	Patients with uncontrolled HTN empaneled to provider	0: < 10% of pts 1: ≥ 10% of pts

*EBP* Evidence-based practice, *BP* Blood pressure, *HTN* Hypertension, *CHW* Community health worker, *EHR* Electronic health records

^1^Time to visit interval will be based on LAC DHS Expected Practice protocols

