### Study participants

#### Clinics

All LAC DHS adult primary care clinics will participate in the trial over the full three-year timeline. We anticipate 27 participating LAC DHS clinics, and plan to recruit an average of 20 providers and 900 patients with hypertension per clinic. The 27 clinics will be grouped into nine sets of three clinics each based on clinic size (large, medium, small) and geographic location as defined by Los Angeles County Service Planning Area [56] (Antelope Valley and San Fernando Valley; San Gabriel Valley and East; Metro, South, and South Bay). Within each set, a masked study statistician will randomize clinics to a study arm using SAS Software Proc Plan [57].

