#### Secondary outcome analyses

To analyze secondary implementation outcomes, we will use a constrained generalized linear mixed-effects model with an appropriate link function to compare the three arms (sequences) at Year 2, using an omnibus test followed by specific comparisons of interest. We will use the same modeling approach to evaluate effects on the health-related outcomes, such as change in hypertension control, at Year 1, and to compare the three arms (sequences) at Year 2. We will also perform adjusted analyses of the above models that include patient- provider-, and clinic-level characteristics.

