#### Sample size and power considerations

The power analysis was performed based on the primary implementation outcome (count, provider EBP adoption). LAC DHS clinics average 20 providers each, and 27 total clinics are expected to be available. Our proposed sample size is expected to achieve > 90% power (or > 80% power) at 5% level of significance to detect an absolute net difference of 1.46 (or 1.24) when comparing changes in primary outcome between no implementation strategy and any implementation strategies at Year 1. The assumptions used in these calculations were: (a) cohort design, (b) event rate of 3, (b) intra-cluster correlation up to 0.05, (c) correlation of 0.3 between repeated visits of providers, (d) overdispersion of 25%, (e) 2-sided test with type-I error rate of 0.05, and (f) attrition rate up to 3% at the end of Year 1. We used the National Institutes of Health sample size calculator for parallel group-randomized trials [76].

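### Clinics are randomised within nine size-by-area sets, but the primary model as written has no term for set, size or area, so the test is conservative if those factors matter

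*Protocol article*

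**What the plan says.** Under Clinics, the protocol article states: "The 27 clinics will be grouped into nine sets of three clinics each based on clinic size (large, medium, small) and geographic location". Size has three levels and area is given as three groups of Service Planning Areas, which fits a three-by-three grid. Allocation follows the sets: "Within each set, a masked study statistician will randomize clinics to a study arm using SAS Software Proc Plan". Three clinics per set and three arms imply nine clinics per arm.

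Under Primary outcome analysis, the model is described in some detail. For the fixed part: "The main fixed effects include a time indicator, a constraint of a common baseline mean across implementation groups, and a group-by-time interaction term". For the random part it lists "random intercepts at bothprovider and clinic levels, as well as a clinic-level time-varying random effect". Set, size and area are in neither list.

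Under Secondary outcome analyses, the article adds: "We will also perform adjusted analyses of the above models that include patient- provider-, and clinic-level characteristics". That sentence suggests that the models described before it are unadjusted. It does not name size or area. The same section applies the same modelling approach to the health-related outcomes.

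The sample size section does not mention the sets.

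**The concern.** A trial that restricts its randomisation would normally carry the restriction into its main model. Randomising within sets removes differences between sets from the arm comparison. A model with no term for the sets still counts those differences as error, so it reports a larger standard error than the design delivers. With nine clinics per arm, the clinic-level part of the error is a large share of the total and cannot be reduced by adding providers.

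The common baseline mean and the clinic intercept already deal with stable differences between clinics. What is at stake is therefore narrower: differences between sets in how much adoption changes by the end of Year 1. If large and small clinics, or the three areas, change at different rates, the trial has controlled for this in its allocation but gains nothing from it in the analysis.

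**Working it through.** **Inputs.** From the sample size section: 27 clinics with 20 providers each, event rate 3, intra-cluster correlation (ICC) 0.05, provider correlation over time 0.3, overdispersion 25%, attrition 3%, two-sided 5%. Detectable net differences are 1.46 (over 90% power) and 1.24 (over 80%).

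Three inputs are assumptions:
- The 25% is read as acting on the SD, so V = 3 × 1.25² = 4.6875.
- The clinic-level correlation over time, rc, is 0.
- R, the share of clinic-level change variance explained by size and area, runs from 0 to 40%.

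**Formula.** With m = 20 × 0.97 = 19.4 providers per clinic, the variance of a clinic's mean change is V × [2(1 − 0.3)(1 − ICC)/m + 2(1 − rc) × ICC].
- Provider part: 4.6875 × 2 × 0.7 × 0.95 / 19.4 = 0.321
- Clinic part: 4.6875 × 2 × 0.05 = 0.469
- Total 0.790, of which the clinic part is 59%
- SE for 9 versus 9 clinics: √(0.790 × 2/9) = 0.419

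**The plan's own figures.** On 16 df, the 80% detectable difference is (2.120 + 0.865) × 0.419 = 1.25, and the 90% one is (2.120 + 1.337) × 0.419 = 1.45. Power is 79.3% at 1.24 and 90.5% at 1.46. This is close to the stated pair but not exact, since 1.46/1.24 = 1.18 while the formula gives 1.16. These settings were chosen because, of many tried, they came closest. Reading the 25% on the variance (V = 3.75) gives 1.12 and 1.30.

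**Without and with the terms.** Three arms leave 27 − 3 = 24 between-clinic df. Size and area main effects use four more, leaving 20. With the terms, the clinic part is multiplied by (1 − R).

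| Model | R | SE | 80% detectable difference |
|---|---|---|---|
| No terms, 24 df | – | 0.419 | (2.064 + 0.857) × 0.419 = 1.224 |
| Size + area, 20 df | 0% | 0.419 | (2.086 + 0.860) × 0.419 = 1.234 |
| Size + area, 20 df | 20% | √((0.321 + 0.375) × 2/9) = 0.393 | 1.159 |
| Size + area, 20 df | 40% | √((0.321 + 0.281) × 2/9) = 0.366 | 1.078 |

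The cost at 0% is 1.234/1.224, or 0.9%. The gain is 5% at 20% explained and 12% at 40%. Break-even solves (2.946/2.921)² × (1 − 0.593R) = 1, giving R of about 0.03.

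**Sensitivity.** The percentage changes do not depend on V. With rc = 0.5 the clinic part falls to 42% of the variance, the difference without terms is 1.026, and with them it is 1.035, 0.991 and 0.944. Gains are then 3% and 8%, and break-even is at 4%. Eight set indicators instead of four main-effect terms (16 df) give 1.251 at R = 0 and 1.174 at 20%, with break-even near 7%.

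**Type I error without the terms.** I simulated normal clinic-mean changes (27 clinics, nine sets, rc = 0, 60,000 trials, pairwise t test on 24 df). The rate was 5.0% at R = 0, 3.7–4.1% at 20% and 2.5–3.3% at 40%. The spread reflects whether the explained variance comes from fixed or random size and area effects, or from a free effect for each set. With the size and area terms in the model and additive effects, the rate stayed at 5%. This is not the generalized Poisson model itself.

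**The case against.** The strongest reply is that the article does not say the terms are excluded. Its list is headed as the main fixed effects, a fuller analysis plan may add to it, and the planned adjusted analyses could cover size and area. This stands in part: the point is about the model as written. But the article sets the model out down to its random effects and places clinic-level adjustment in further analyses, so someone following the text would leave the sets out.

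It is also fair that the gain is conditional. No share is given, and below about 3% the terms cost slightly more than they return.

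Some stronger readings are tempting and are not supported:
- A reader might infer that the omission biases the result or undermines the power statement. In a balanced design the estimated effect is the same with or without the terms, and the stated "> 90% power (or > 80% power) at 5% level of significance" claims no gain from the sets.
- A reader might infer that a mixed model on 27 clusters will be tested against a normal reference and so exceed 5%. The article names no reference distribution, and the effect of omitting the sets runs in the opposite direction.
- A reader might infer that the trial judged size and area to be prognostic. The article says only that clinics are grouped on them and gives no reason.

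**Conclusion.** The point holds in a limited form. Randomisation is within nine size-by-area sets, and the primary model as written has no matching term. The consequence is a conservative test and unused precision, not bias and not false-positive inflation. Over an assumed 0–40% explained share, type I error is about 5% falling to about 3%. The 80% detectable difference with the terms runs from 0.9% worse to 12% better than 1.22.

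The absolute figures rest on reading overdispersion on the SD and on rc = 0. The percentage gains shrink if clinic effects are correlated over time. This is an inexpensive improvement to the primary analysis, and the trial remains valid without it.

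**What to change.** In the primary model and the health-outcome models, include clinic size (three levels) and area (three levels), each with its interaction with time. A set-by-time random effect is an alternative. Test the arm-by-time contrasts on between-clinic degrees of freedom (about 20 with the four added terms), or by permuting arms within the nine sets. State this in the primary analysis text, not only among the adjusted analyses.

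The cost is wording, since size and area were already used to form the sets. The statistical price is four between-clinic degrees of freedom, under 1% in detectable difference if the factors explain nothing. Main effects are preferable to eight set indicators, which use twice the degrees of freedom and need about 7% explained variance to pay for themselves.

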**Fig. 1 Fig1:**
[figure not shown]
Three-arm, cluster randomized crossover design

Arm 1: Usual implementation strategies in Year 1 followed by both patient-focused and provider-focused strategies in Year 2Arm 2: Patient-focused strategies in Year 1 followed by provider-focused strategies in Year 2Arm 3: Provider-focused strategies in Year 1 followed by patient-focused strategies in Year 2

Table 2 lists our study aims and hypotheses. The trial was registered in ClinicalTrials.gov (NCT06359691) and was approved by the Olive View-UCLA Education and Research Institute Institutional Review Board (#2,097,481), with reliance agreements with UCLA (#24–5057), Los Angeles County Department of Public Health (#10,136), RAND (#2024-N0071), and University of Southern California (#UP-24–0093).

**Table 2 Tab2:** Primary and Secondary Study Aims

Aim Type	Aim	Hypothesis
Primary Implementation Aim	To test the effectiveness of the implementation strategies (usual implementation, patient-focused, and provider-focused) on change in adoption of EBPs at end of Year 1	Compared to usual implementation strategy (Arm 1), provider- or patient-focused implementation strategies (Arms 2 or 3) will exhibit greater increase in overall provider adoption of EBPs
Secondary Implementation Aim 1	To examine the impact of the sequence of the implementation strategies (usual implementation followed by both provider- and patient-focused; patient-focused followed by provider-focused; provider-focused followed by patient-focused) on change in EBP adoption at end of Year 2	Provider-focused followed by patient-focused implementation strategies (Arm 3) is expected to show greater increase in provider adoption of EBPs compared to usual implementation followed by both (Arm 1)
Secondary Implementation Aim 2	To examine the impact of the sequence of the implementation strategies on secondary implementation outcomes of EBP acceptability, appropriateness, and feasibility	Provider-focused followed by patient-focused implementation strategies (Arm 3) compared to usual implementation followed by both (Arm 1) is expected to show greater increase in secondary implementation outcomes
Health-Related Aim 1	To test the effect of the implementation strategies (usual, patient-focused, and provider-focused) on change in HTN control at end of Year 1	Provider- or patient-focused strategies (Arms 2 or 3) are expected to show greater increase in patient’s HTN control, compared to usual implementation (Arm 1)

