#### Patient outreach

Patients with uncontrolled hypertension empaneled to clinics in the patient-focused strategy arm will receive messages through the patient portal or via text message. All messages contain a link to the culturally and linguistically tailored hypertension education materials described above. In addition, patients who have no primary care or nurse-directed hypertension clinic appointment scheduled within the next three months, or missed a primary care or nurse-directed hypertension clinic appointment within the last three months, will receive the following message: “Your care team needs to check your blood pressure and has saved an appointment for you. This visit is important to keep you healthy. Call *[clinic phone number]*to schedule your appointment within the next 3 months.” By stating, “Your care team has saved an appointment for you,” this message aims to increase clinic visits based on behavioral science insights that telling patients something is reserved for them enhances perceptions of selectivity and influences choice [62, 63]. We will send a follow-up message one week later, with up to three total messages per patient. For patients who do not complete a blood pressure management appointment after three messages, internal facilitators will conduct phone outreach to support scheduling.

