### Provider-focused strategies

Care teams in clinics assigned to the provider-focused strategies will receive training to increase awareness about EBPs and provide guidance in their use (Table 3).

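### Two of the nine primary-score items can record delivery of the allocated strategy, so an active arm could gain up to one point in Year 1 with no change in hypertension care

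*Protocol article*

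**What the plan says.** Table 5 (Primary outcome analysis) defines nine items of one point each. The primary hypothesis in Table 2 is that the active arms "will exhibit greater increase in overall provider adoption of EBPs" than usual strategy at the end of Year 1.

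- **Item 8** is "Uptake of HTN education and training". One class is enough for the point, and the source is course participation and CME requests. Under Provider-focused strategies: "Care teams in clinics assigned to the provider-focused strategies will receive training to increase awareness about EBPs". In Table 3, webinars appear in the provider-focused column and never in the usual column.
- **Item 5** is "Referral of patients to HTN resources (via texts, portal, mailings, phone calls"). It is scored when at least half of a provider's patients with uncontrolled hypertension are referred. Under Patient outreach: "Patients with uncontrolled hypertension empaneled to clinics in the patient-focused strategy arm will receive messages through the patient portal or via text message". Every such message links to the tailored materials. Patients who still have not completed a blood pressure visit after three messages are telephoned by internal facilitators.

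The Outcomes section lists Patient Outreach Center data, the patient portal and training registration logs among the sources of the score. The abstract also names webinar participation as a source.

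The power statement reads: "expected to achieve > 90% power (or > 80% power) at 5% level of significance to detect an absolute net difference of 1.46 (or 1.24"). The contrast it refers to sets Year 1 change without a strategy against Year 1 change with any strategy.

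**The concern.** The trial asks whether the strategies lead providers to adopt hypertension practices. An outcome item that is scored when the strategy is received cannot be evidence that the strategy worked.

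In Year 1, Arm 3 is given training and Arm 2 has its patients messaged. Arm 1 is given neither by the study. Item 8 then tends to separate Arm 3 from Arm 1, and item 5 may separate Arm 2 from Arm 1, because of allocation itself. For item 5 the provider may have to do nothing, since Table 3 has the study team sending the registry reminders.

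The protocol elsewhere treats training as strategy delivery: the implementation-progress tool tracks staff training, and Table 4 lists that tool under delivery of strategies, apart from adoption. A significant primary result could therefore arise while the other seven items do not move. If there is a true effect, the estimate would be inflated by the delivery component.

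This concerns the Year 1 comparison with usual strategy. It is not directed at the Year 2 comparison of sequences.

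**Working it through.** **Inputs.** From Sample size and power considerations: "LAC DHS clinics average 20 providers each, and 27 total clinics are expected to be available"; event rate 3; intra-cluster correlation (ICC) 0.05; correlation 0.3 between repeated visits; overdispersion 25%; two-sided 5%; attrition 3%. From Study participants: nine sets of three clinics, hence 9 clinics per arm. From Table 5: one point per item.

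**Step 1: reproduce the stated power.** For a difference in change of size d, with m = 20 × 0.97 = 19.4 providers per clinic:

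SE² = 2 × [ICC + (1 − ICC)(1 − r)/m] × [1.25 × 3/9 + 1.25 × (3 + d)/9]

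The first factor is 2 × [0.05 + 0.95 × 0.7/19.4] = 0.1686. At d = 1.24 the second is 0.4167 + 0.5889 = 1.0056, so SE = √(0.1686 × 1.0056) = 0.412 and d/SE = 3.01. With 16 df (critical value 2.120), power is 80.7%. At d = 1.46 it is 90.6%. Both agree with the stated values. With 9 against 18 clinics the same formula gives 93.0% and 97.8%. So the stated figures fit one active arm against usual, although the article does not say which contrast was powered.

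**Step 2: cross-check the SE from the stated pairs.**
- Normal: 1.24/(1.960 + 0.842) = 0.443 and 1.46/(1.960 + 1.282) = 0.450.
- t, 16 df: 1.24/(2.120 + 0.865) = 0.415 and 1.46/(2.120 + 1.337) = 0.422, mean 0.419.

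**Step 3: size of the built-in gain.** The gain on an item is the share of providers scoring it in the active arm minus that share in Arm 1. Its ceiling is 1.0, which is 1.0/1.24 = 81% of the difference detectable at 80% power. The article gives neither share, so a range is needed.

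**Step 4: chance of a significant result favouring one active arm when only the delivery item moves.**

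| Gain | Formula of Step 1 | Noncentral t, SE 0.419 | Normal, SE 0.443 / 0.450 |
|---|---|---|---|
| 0 | 2.5% | 2.5% | 2.5% |
| 0.3 | 10.0% | 9.9% | 10.0% / 9.8% |
| 0.5 | 20.7% | 20.1% | 20.3% / 19.8% |
| 0.8 | 45.5% | 43.4% | 43.9% / 42.7% |
| 1.0 | 63.5% | 61.1% | 61.8% / 60.3% |

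Worked at 1.0: SE = √(0.1686 × 0.9722) = 0.405; 1.0/0.405 − 2.120 = 0.35; probability 63.5% on 16 df.

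If both active arms have the same gain and are each tested against the shared Arm 1 (simulation, SE 0.419, 24 df), at least one is significant in about 78%, 61% and 32% of trials at gains of 1.0, 0.8 and 0.5.

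**Step 5: sensitivity to the contrast.** If 1.24 and 1.46 were meant for both active arms pooled against usual, the one-arm figure at a gain of 1.0 falls to about 49 to 50%.

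**Step 6: after removing items 5 and 8.** The built-in gain is zero, and the chance in favour of the active arm returns to 2.5%. If the event rate falls in proportion, 3 × 7/9 = 2.33 (an assumption), the Step 1 formula gives detectable differences of about 1.10 (80% power) and 1.29 (90%) on the 0 to 7 scale.

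**The case against.** The best defence has five parts.

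1. *Training is partly practice content.* In Table 3, practice 3 includes clinicians trained on the measurement protocol, and practice 6 was adapted to include staff training. That stands: it would be too flat to say that training lies outside the evidence-based practices. Item 8, however, is met by a single class, and the classes the protocol describes are the strategy.
2. *Attendance is a provider's own act.* It is encouraged and not required, so item 8 records receipt and not mere offer. That stands too, and it is why 1.0 is only a ceiling for Arm 3. Usual-arm providers may also score, because the item is not limited to study webinars and recordings sit on a system-wide platform.
3. *Item 5 may not count study messages.* It is worded as referral, it relates to practices 1 and 6, and no rule says that study-sent messages qualify. Table 3 also says only that patients may receive materials. So the Arm 2 half is conditional. The match of channels and patients, and the data sources listed, still point towards counting them.
4. *The overlap is disclosed and the trial is a Type 3 hybrid.* Disclosure in the abstract does not separate delivery from effect, and the hypothesis is about increased adoption.
5. *The primary score is registered and was developed with the funder's statisticians.* This is a fair reason for a lighter remedy than outright replacement.

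A reader might infer that each active arm will gain a full point, or that the false-positive rate is about 61%. The documents support neither. No rates are given, and if delivery truly raises the score, the null hypothesis for that score is false. The problem is what the score measures, not the size of the test.

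**Conclusion.** The point holds in a qualified form. Item 8 records receipt of the provider-focused strategy. Item 5 records delivery of the patient-focused strategy if study-sent messages count. The Year 1 contrast with usual strategy is then partly circular, and nothing else in the article removes this.

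The built-in gain is at most one point per active arm. Its consequence runs from about a 10% chance of a significant result at a gain of 0.3 to 60 to 63% at the ceiling, compared with 2.5% in that direction with no gain. This rests on reading the stated power as 9 against 9 clinics, which the reproduction supports, and on unknown item rates. A gain near 1.0 is more plausible for Arm 2, where all uncontrolled patients are to be messaged, than for Arm 3, where it depends on attendance.

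As scored, a positive primary result would not by itself show that provider care changed.

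**What to change.** 1. State whether study-sent messages count under item 5. Either exclude them or treat item 5 as a measure of strategy delivery.
2. Report items 5 and 8 separately, by arm, as delivery measures.
3. Pre-specify the Year 1 contrast on items 1 to 4, 6, 7 and 9 (range 0 to 7). Preferably make this the primary score and keep the nine-item score as secondary. If the registered score is kept as primary, make the seven-item contrast a key analysis that must support any claim that the strategies changed provider adoption.
4. Restate the event rate and detectable difference on the 0 to 7 scale, and say whether the power is for one active arm or for both pooled.

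Cost: no new data, a re-run of the power calculation, and a registry update if the primary score changes. The shorter score has fewer items, may show a smaller difference, and loses the item closest to the education-materials practice unless item 5 is kept with study messages excluded.
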